## Abstract

**Background:**

Urinary incontinence following acute stroke is common, affecting between 40%-60% of people in hospital after a stroke. Despite the availability of clinical guidelines for urinary incontinence and urinary incontinence after stroke, national audit data suggest incontinence is often poorly managed. Conservative interventions (e.g. bladder training, pelvic floor muscle training and prompted voiding) have been shown to have some effect with participants in Cochrane systematic reviews, but have not had their effectiveness demonstrated with stroke patients.

**Methods/Design:**

A cluster randomised controlled pilot trial designed to assess the feasibility of a full-scale cluster randomised trial and to provide preliminary evidence of the effectiveness and cost-effectiveness of a systematic voiding programme for the management of continence after stroke. Stroke services will be randomised to receive the systematic voiding programme, the systematic voiding programme plus supported implementation, or usual care. The trial aims to recruit at least 780 participants in 12 stroke services (4 per arm). The primary outcome is presence/absence of incontinence at six weeks post-stroke. Secondary outcomes include frequency and severity of incontinence, quality of life and cost-utility. Outcomes will be measured at six weeks, three months and (for participants recruited in the first three months) twelve months after stroke. Process data will include rates of recruitment and retention and fidelity of intervention delivery. An integrated qualitative evaluation will be conducted in order to describe implementation and assist in explaining the potential mediators and modifiers of the process.

**Trial Registration:**

ISRCTN: ISRCTN08609907

## Background

Urinary incontinence following acute stroke is common, affecting between 40%-60% of people in hospital after a stroke; 25% at hospital discharge and 15% after one year [1]. In longer term stroke survivors, the prevalence has been reported as 17% [2]. Urge incontinence is the most common type after stroke [3], but the cerebral lesion may also lead to practical difficulties with bladder control caused by, for example, motor impairment, depression and aphasia [4] (termed functional incontinence). Despite the availability of clinical guidelines for the management of urinary incontinence in general [5] and urinary incontinence after stroke [6], national audit data [7] suggest incontinence is often poorly managed.

Our systematic review [8] found no rigorously conducted studies evaluating interventions designed to manage urinary incontinence after stroke in secondary care. The intervention in our programme will focus on conservative strategies shown to have some effect with participants in studies included in Cochrane systematic reviews [9-13], but which have not had their effectiveness demonstrated with stroke patients. These strategies are a combined package of bladder training and (where possible) pelvic floor muscle training, and prompted voiding.

Available conservative interventions for urinary incontinence include bladder training, timed voiding, prompted voiding, habit retraining and pelvic floor muscle training. Bladder training is generally used for urge incontinence and aims to increase the time interval between voids so continence is regained. It involves patient education, scheduled voiding, and positive reinforcement, but can also include self-monitoring and urge suppression techniques. Prompted voiding and timed voiding have mainly been used with people who have cognitive deficits. They are based on a system of scheduled voids, with prompted voiding including reminders and reinforcement for self-initiation of toileting. To date, trials of prompted voiding have mainly taken place in United States nursing homes; however there is no a priori reason why this approach should not be introduced into the care of stroke patients in secondary care in the UK.

Pelvic floor muscle training may also be effective in assisting the individual to manage urge, stress or mixed incontinence [10], and has been shown to be effective as a combined intervention with bladder training [14,15].

The effectiveness of conservative interventions has been systematically reviewed in adults. In the review of bladder training [11], trials tended to favour bladder training and there was no evidence of adverse effects. The review of prompted voiding [9] found evidence of increased self-initiated voiding and decreased incontinent episodes in the short-term.

Despite a growing evidence-base, existing evidence has not been widely implemented in clinical practice, even by stroke specialist teams working on recognised stroke units [16]. This lack of implementation in stroke clinical practice is in keeping with a recent and growing recognition that the implementation of research in practice is influenced not only by individual clinicians but also by the organisational context in which they operate [17-22]. Organisational context has been defined as "the environment or setting in which the proposed change is to be implemented" [23]. At its simplest level, context may refer to the physical environment where health care takes place. However, Rycroft-Malone et al. concluded from their concept analysis that contexts conducive to research implementation included a range of less tangible process elements: "clearly defined boundaries; clarity about decision-making processes; clarity about patterns of power and authority; resources; information and feedback systems; active management of competing "force fields" ... and systems in place that enable dynamic processes of change and continuous development.' [23].

Theories underpinning organisational influence include those of learning organisations (with characteristics encompassing hierarchical structure, information systems, human resource practices, organisational culture and leadership [24]) and knowledge management (how organisational mechanisms affect knowledge uptake and use [25-27]). Successful implementation of an intervention to improve the management of post-stroke urinary incontinence is likely to be mediated not only by individual members of staff and availability of evidence-based guidance, but also by the complexity of the intervention as well as the interplay of patient, social and organisational factors [28,29]. Careful attention needs to be paid to the specific barriers to change in any given setting, identified through 'diagnostic analysis' [30] at levels that may include the individual, groups or teams, organisations and the wider healthcare system [31]. Strategies then need to be 'tailored' to overcome barriers identified [32].

We therefore plan to evaluate whether supported implementation, through targeted organisational development aimed at 'normalising' the intervention [33-35], is more effective than introduction of the intervention alone, as well as evaluating both in comparison to usual care.

### Aim

The trial aims to assess the feasibility of a full-scale cluster-randomised trial: to test the interventions for preliminary evidence of clinical effect and to provide information to enable estimates of the number of sites and patients that would need to be recruited for a full-scale cluster-randomised trial to evaluate effectiveness.

### Objectives

The trial objectives are to:

• assess feasibility in terms of rates of participant recruitment and retention

• assess fidelity to the intervention

• conduct a qualitative assessment of feasibility from the perspective of multiple stakeholders

• conduct a preliminary evaluation of supported implementation compared with implementation alone

• investigate patient-related factors affecting patient outcome

• investigate stroke service-level factors potentially affecting stroke service outcomes to estimate the amount of unexplained variability in outcomes between Trusts and between patients

• confirm the choice of primary and secondary outcome measures for a full-scale cluster-randomised trial to evaluate effectiveness

• develop and test data collection tools for an economic evaluation within a full-scale cluster-randomised trial

### Design

A three arm, parallel, open, exploratory, pragmatic, cluster-randomised controlled trial of a systematic voiding programme (including bladder training and pelvic floor muscle training for patients who are cognitively able and prompted voiding for patients with cognitive impairments), with or without supported implementation, for the management of urinary incontinence after stroke in secondary care.

## Methods

### Study setting

Twelve NHS stroke services in England and Wales. For the purpose of the trial, a stroke service will comprise both acute and rehabilitation stroke units. Stroke units will be defined according to the definition provided by the Royal College of Physicians of London for the National Sentinel Stroke Audit [7].

#### Inclusion criteria for stroke services

Stroke services with specialist acute and rehabilitation stroke services (either separate or combined units).

Access to appropriate Excess Treatment and Service Support costs.

#### Exclusion criteria for stroke services

Stroke service without specialist acute and rehabilitation stroke units (either separate or combined).

#### Inclusion criteria for patients

Patients aged 18 or over who have a diagnosis of stroke based on the WHO criteria [36] will be included in the study, with no upper age limit. Patients are required to have urinary incontinence (UI) as defined by the International Continence Society [37] as "involuntary loss of urine" and to have incontinence classified as stress UI, urge UI, mixed UI or 'functional' UI **OR **to be catheterised in the acute phase of the stroke; to be conscious (defined as either 'alert' or 'drowsy' on the 'Clinical Status on Admission' item of the European Stroke Database), and to be medically stable as judged by the clinical team.

Participants who had incontinence before the index stroke will be included. Given the expected age range of the population, there is likely to be a high prevalence of pre-stroke incontinence among potential participants. Furthermore, there is evidence to suggest patients with longstanding incontinence may benefit from a programme of behavioural interventions [9,11].

Participants who are catheterised will be recruited; if the catheter is removed, they will be assessed as per protocol and begin the systematic voiding programme if they are still incontinent. Participants who are continent after catheter removal and those discharged with a catheter still in situ will not be put onto the programme. Data from these participants will be analysed separately from participants who have taken part in the programme.

#### Exclusion criteria for patients

Patients who refuse consent.

Patients unable to consent for whom a consultee does not agree that the patient would wish to be included.

### Centre recruitment process

The trial has been adopted onto the Stroke Research Network (SRN) portfolio and was identified as open to new sites using SRN procedures. The research team also made contact with all stroke services in the North West of England and Wales and invited expressions of interest.

### Patient recruitment process

Patients who meet the inclusion criteria will be approached as early as possible following admission to the participating stroke unit. Patients who do not meet the inclusion criteria early post-stroke will be approached as soon as possible if they subsequently meet the inclusion criteria. Nursing staff will ask each eligible patient whether his/her name can be given to the research team. If the patient agrees, a member of the research team will visit the patient, explain the project, answer any questions they may have and provide an information leaflet. Patients will be given at least 24 hours to consider participation and will be visited by a member of the research team after this period; patients choosing to participate will sign the consent form at this stage.

For patients unable to consent for themselves, a person able to advise on the presumed wishes of the patient will be approached to act in the role of consultee. This is in line with the recommendations of the Mental Capacity Act [38] and in line with the expressed wishes of the study Patient, Public and Carer Involvement groups, who would like everyone who is eligible to have the opportunity to participate.

Recruitment rates in each cluster will be monitored on a monthly basis to identify both quantitative (i.e. numbers of participants recruited) and qualitative (i.e. patient characteristics) imbalance across clusters [39]. Should identified imbalance be indicative of likely selection bias (e.g. cluster with low proportion of stroke patients identified as eligible but high proportion of those eligible with severe incontinence), we will review the recruitment process and address any issues identified.

### Centre randomisation

#### Sequence generation

Stroke services will be placed into four strata based, in order of priority, on (i) whether they have separate or combined acute and rehabilitation units (ii) their average performance on the 'nine key indicators of stroke care' in the National Sentinel Stroke Audit Phase II (clinical audit) [7] (iii) the number of stroke patients admitted per year. Services will be randomly allocated to intervention (n = 4), intervention plus supported implementation (n = 4) and usual care (n = 4) groups by the Clinical Trials Unit at Newcastle University. After allocating hospitals to the strata, the randomisation schedule will be generated using block randomisation (block length of 3) to allocate one site to each arm within every stratum. The software package STATA (version 9) will be used.

##### Allocation concealment

Within each stratum, stroke services will not be informed as to their intervention allocation until ALL stroke services within that stratum are recruited to take part in the trial. However, services will then be aware of their allocation, as will staff identifying and recruiting trial participants from within that service.

### Interventions

#### Systematic voiding programme

The intervention will comprise algorithm-driven individualised systematic voiding programmes tailored to the physical and cognitive capabilities of each patient The algorithm specifies two routes: a combined package including bladder training and pelvic floor muscle training for those patients who are cognitively able, and prompted voiding for those with cognitive impairment. Bladder training will include three main components: 1) focused education for patients and carers (including information on the anatomy and physiology of the lower urinary tract, the rationale behind the programme and strategies to suppress the urge to void, for example distraction and relaxation [15,40]); 2) individualised voiding regimens designed to restore normal voiding patterns by progressively lengthening the time interval between voids, based on assessment of participants' normal voiding patterns and self-monitoring; 3) patient-held voiding diary, a cognitive intervention designed to promote self-awareness of voiding habits [41,42].

Pelvic floor muscle training is designed to strengthen types I and II muscle fibres in the pelvic floor. Patients will be instructed to perform 5 fast (3 seconds) and 10-20 sustained (10 seconds) contractions with 10 second relaxation periods between contractions twice a day.

For those patients with cognitive impairments, the programme will consist of elements traditionally classified as prompted voiding: participants will be approached according to individualised schedules (for example every two hours during waking hours), asked if they are wet or dry, and prompted to use the toilet [43]. Verbal praise will be offered for correct reporting of dryness/wetness and successful toileting. Participants with cognitive impairments will be given the opportunity to participate in the education and patient-held diary components of the intervention.

Participants not able to walk to the toilet will be assisted by nursing staff. Participants will be provided with written information about their systematic voiding programme to enable them to continue with it after discharge from hospital.

The intervention has been informed by the findings of an evidence synthesis on the barriers and enablers to successful implementation of conservative interventions for UI completed during the programme's Development Phase, in line with the MRC Framework for developing and evaluating complex interventions [44,45].

The systematic voiding programme will be incorporated into routine practice by all staff in day-to-day contact with patients. All nursing staff (including health care assistants, night staff and student nurses) will be provided with an education programme of both theory and practice. Training will be largely web-based to facilitate easy access and flexibility, but face-to-face sessions will also be offered to cover the practical aspects of intervention delivery and recording.

#### Systematic voiding programme plus supported implementation

Services randomised to the supported implementation arm of the trial will receive the systematic voiding programme together with supported implementation comprising: diagnostic analysis of context at the level of the organisation and the individual, identification of barriers (defined as "factors that impede the implementation of change in professional practice" [32]) and facilitators to the intervention, as well as targeted organisational development activities.

To support the process of implementing the systematic voiding programme, we will use a form of facilitation, a model that has been used successfully in secondary care settings [46,47]. The process of facilitation involves supporting and enabling people to change their practice [46-48]. Although approaches to facilitation vary, they are based on the principle that ownership is with the group [49]. The facilitator guides the group towards accomplishing a goal, helping members identify the obstacles that may impede progress and enabling members to identify strategies to overcome them [50]. While there will be a focus on goal attainment (defined as the normalisation of the systematic voiding programme [35]), our approach to facilitation will primarily focus on 'enabling' rather than 'doing for' others [47] with an emphasis on developing and empowering both individuals and teams. Experienced external facilitators will work with nominated internal facilitators in each site; further details of the supported implementation intervention are available on request from the lead author.

#### Usual care (control group)

Participants in this group will receive usual care provided by the stroke service. This may comprise: checking for urinary tract infection; checking for overflow incontinence (bladder scanners will be provided); containment using a variety of devices (for example absorbent products) with regular changes and some form of toileting schedule.

### Outcomes

#### Effectiveness

The primary effectiveness outcome will be incontinence (presence; absence). Measures will be taken at 6 weeks, 3 months and, for those recruited during the first three months, 12 months post stroke. The primary analysis will be of the 6-week data as conservative interventions for continence typically last six weeks [11,15], and an effect is most likely to be seen at this time point.

Secondary effectiveness outcomes will be: quality of life, frequency and severity of incontinence, urinary symptoms, activities of daily living (ADLs), and death; at 6 weeks, 3 months and, for those recruited during the first three months, 12 months post stroke.

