In addition, the following baseline information about the patient will be recorded following consent: date of birth (age to be calculated*); sex; ethnicity; date of admission; date of stroke onset; date baseline questionnaire completed; location when recruited into the study; consciousness level (defined as either 'alert' or 'drowsy' on the 'Clinical Status on Admission' item of the European Stroke Database); side of body affected by stroke; type of stroke; location of stroke (OCSP classification[59]); co-morbidities (Charlson Comorbidity Index[60]; day seven Barthel Index [58]; pre-stroke Modified Rankin Scale [61]*; pre-stroke living circumstances*; Leicester Urinary Symptom questionnaire [57]; type of UI (urge UI, mixed UI, 'functional' UI or unclear); cognitive ability (6 Item Cognitive Impairment Test [62]); fluid intake; bowel function; relevant clinical investigations (e.g. mid stream urine, bladder scan); medications; living circumstances; verbal sub-section of the Glasgow Coma Scale [63]*; ability to lift both arms off the bed*; ability to walk independently*; ICIQ-UI Short Form [51]; Incontinence Severity Index [56]; EuroQol (EQ-5D) [55].

The six factors highlighted with a * above from the Edinburgh stroke case mix adjuster [64] will be collected to enhance patient-level adjustment for prognosis.

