#### Outcomes

The primary analysis set will be defined as the intention-to-treat population. All stroke services randomised will be retained in the trial. Outcome data will be collected from all consented patients whenever possible, whatever their level of subsequent engagement with the allocated intervention programme. If there is more than 10% loss to follow-up overall or moderately differential loss to follow-up across stroke services, a secondary per-protocol analysis will also be considered. The decision as to whether a per-protocol analysis will be informative will be made by the trial statistician in conjunction with other members of the Trial Management Group; this decision will be made without reference to the recorded values of the outcome data.

To account for the cluster randomisation, we shall use mixed effects modelling for continuous, ordinal and dichotomous outcomes to compare the two groups on primary and secondary outcome data. Baseline measures of the outcomes variables (where appropriate), stroke classification, type of incontinence and the other prognostic patient-level information (from the Edinburgh case-mix adjuster) will be included as individual-level covariates in the models for outcome data.

Missing outcome data will be imputed according to the particular outcome. For the primary analysis, dichotomous and ordinal outcomes for those who withdraw, die or are otherwise lost to follow-up will be imputed using a worst-case scenario (e.g. for the primary outcome variable, all those for whom incontinence status is not recorded at 6-weeks post-stroke will be assumed to be incontinent). For continuous outcomes, the primary analysis will use a non-parametric multiple imputation approach [66].

The effect of stroke service-level factors will also be explored in the modelling; this will enable appropriate stratification to be used in the future larger scale trial, if desired, and to potentially reduce the size of the intra-stroke service correlation coefficient by reducing the unexplained component of the variability between stroke services. This analysis will be used to confirm the sample size necessary for the future trial and to provide estimates (including 95% confidence intervals) of the effectiveness of each intervention relative to usual care.

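### The 6-week primary time point is justified by treatment length but counted from stroke, with no limit on time to recruitment and no listed adjustment for time since stroke

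*Protocol article*

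**What the plan says.** All references are to the protocol article.

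- **Outcomes, Effectiveness.** The clock starts at stroke: "Measures will be taken at 6 weeks, 3 months and, for those recruited during the first three months, 12 months post stroke". Two reasons are given for making week 6 primary: "The primary analysis will be of the 6-week data as conservative interventions for continence typically last six weeks", and "an effect is most likely to be seen at this time point".
- **Inclusion criteria for patients.** Entry requires incontinence or acute-phase catheterisation, consciousness and medical stability. No maximum time since stroke is set. For catheterised recruits, "if the catheter is removed, they will be assessed as per protocol and begin the systematic voiding programme if they are still incontinent".
- **Patient recruitment process.** Early approach is the aim, but later entry is allowed: "Patients who do not meet the inclusion criteria early post-stroke will be approached as soon as possible if they subsequently meet the inclusion criteria". On consent, "Patients will be given at least 24 hours to consider participation".
- **Allocation concealment.** Staff who identify and recruit participants know their service's allocation.
- **Ascertainment of outcomes.** The baseline record includes "date of stroke onset; date baseline questionnaire completed".
- **Data analysis, Outcomes.** The individual-level covariates are baseline values of the outcomes, stroke classification, incontinence type and the Edinburgh case-mix factors. For the primary outcome, "all those for whom incontinence status is not recorded at 6-weeks post-stroke will be assumed to be incontinent".

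**The concern.** The first reason for week 6 concerns how long treatment lasts, whereas the time point is defined by how long ago the stroke was. The two would agree only if the programme began on the day of the stroke, which the entry process rules out.

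Three things follow. First, exposure at the primary assessment is shorter than the rationale suggests and varies between participants, so the pilot's effect estimate, which is meant to inform a full trial, needs to be read with that in mind. Second, a patient still incontinent several weeks after stroke is plausibly in a different prognostic position from one incontinent in the first days. If services in different arms recruit at different speeds, and staff who know the allocation could do so, part of a difference between arms may reflect timing. With four services per arm, one or two unusual services could matter. Third, a participant who enters after week 6 has no 6-week status to record, and the imputation wording would count that participant as a failure.

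**Working it through.** **1. Clock against rationale.** The assessment falls at day 42 after stroke. If the programme starts *d* days after stroke, possible exposure is

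E = max(0, 42 − d).

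A patient who consents in person has at least one day to decide, so d ≥ 1 and E ≤ 41 days, before any time for admission, stabilisation or assessment. The article states no waiting period for the consultee route, but entry there also follows admission and medical stability, so E is still below 42. No participant in an active arm can have had six full weeks of the programme.

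**2. Range of *d*.** The article sets a lower limit in effect and no upper limit. Later eligibility can delay recruitment. Catheterisation does not delay recruitment, since it is itself a route to eligibility, but it delays the start of the programme. Under assumed delays of 7, 14, 21 and 28 days, E is 35, 28, 21 and 14 days. These are days of possible exposure, not shares of a treatment effect.

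**3. Can the number with no exposure be found?** Not from the document. To show how much depends on the assumption, suppose the delay is lognormal with median *m* days and log-scale standard deviation *s*. The share at or beyond day 42 is

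1 − Φ(ln(42/m)/s).

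- m = 5, s = 0.6: 1 − Φ(2.128/0.6) = 1 − Φ(3.55) ≈ 0.0002, which is fewer than 1 of the planned 780.
- m = 14, s = 0.9: 1 − Φ(1.099/0.9) = 1 − Φ(1.22) ≈ 0.111, which is about 87 of 780.

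The medians and spreads are assumptions, and the result runs from negligible to material. The aim of early approach makes the low end more plausible, but nothing in the article settles it.

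**4. Is time since stroke in the model?** The six starred Edinburgh factors are age, pre-stroke Rankin score, pre-stroke living circumstances, the verbal part of the Glasgow Coma Scale, arm lift and independent walking. None is time since stroke, nor are the other listed covariates. Both dates needed to derive it are collected, and the Data collection section places baseline on entry to the trial, so baseline date can stand for recruitment date.

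**5. The imputation rule.** The sentence starts from participants who withdraw, die or are otherwise lost, but its example extends to everyone without a recorded 6-week status. Someone recruited after day 42 fits the example and not the opening. That person's baseline values would also post-date the outcome they are meant to adjust.

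**The case against.** The case for the plan is substantial.

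- **The endpoint is consistently defined.** Six weeks after stroke is used throughout. The remark about six weeks describes the literature on such interventions and promises nobody 42 days of treatment. This stands: the fault lies in the reason given, not in the definition.
- **A common post-stroke clock has merit.** It compares arms at the same point in spontaneous recovery. A reader might infer that the endpoint should be timed from recruitment instead. The document does not support that step: a difference in recruitment delay between arms would then become a difference in recovery time at the primary assessment, and the Background shows incontinence becoming less common with time.
- **Dilution cannot be quantified.** A reader might convert the exposure days above into a percentage loss of effect. That needs both a delay distribution and even accrual of benefit over 42 days, and the article gives neither. In a pragmatic intention-to-treat comparison, delay before starting is also partly what the service delivers.
- **Adjustment is not absent.** Baseline continence, arm lift and walking are recorded after consent and carry some information about status at entry. Recruitment numbers and patient characteristics are monitored by cluster. So calling time since stroke a wholly uncorrected confounder would overstate the case. The adjustment is still partial, and recruitment timing is not named in the monitoring.
- **Late entrants are hypothetical.** No section describes anyone recruited after week 6, and participants who are recruited with a catheter and never go onto the programme are analysed separately. That separate analysis does not cover late recruits, and the imputation wording still reaches them.
- **The analysis plan, not shown, may add the covariate.** It may. The article nevertheless gives its own list, and the mismatch between clock and rationale does not depend on that plan.

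**Conclusion.** The point holds in a limited form. The stated rationale does not fit the post-stroke clock: possible exposure at the primary assessment is under six weeks for everyone and varies by an amount the article does not allow to be computed. Time since stroke is left out of a stated covariate list although the data are held, and the missing-data wording, taken literally, scores as incontinent anyone whose assessment fell due before entry.

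The prognostic role of time since stroke is a plausible assumption. The Background's falling prevalence figures (40%-60% in hospital, 25% at discharge, 15% at one year) are consistent with it, but they do not give the outlook for a patient still incontinent at a particular day. A difference in timing between arms is possible because recruiters are unblinded; the article does not show that one will occur. This does not invalidate the endpoint. It is a low-cost improvement to a pilot whose estimates are meant to inform the full trial.

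**What to change.** Keep the common post-stroke clock and make four changes:

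1. Add days from stroke onset to recruitment (baseline) as an individual-level covariate in the primary model, in all three arms.
2. Summarise that interval by arm and by cluster.
3. State that a 6-week outcome whose due date preceded recruitment is not imputed as incontinent, and report the number of such participants by arm.
4. Reword the rationale in the Effectiveness section so that it does not imply six weeks of programme exposure.

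The first two need no new data, since both dates are already recorded. The last two are changes of wording plus one reported count. The statistical cost is one extra model parameter.
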